### Design of the trial

Sixty women with idiopathic mild CTS will be evaluated at before (baseline), 1, 6 and 12 months after injection.

The major outcome of this study is to determine that locally-injected progesterone may be more beneficial than cortisone in carpal tunnel syndrome at clinical level (SSS-BQ, VAS). Secondary outcome measures are:

- duration of experimental therapy, with a short (after 1 month) and long follow-up (after 6 to 12 months);

- improvement of electrodiagnostic and ultasonographic anomalies at various follow-up;

- correlation of the neurophysiologic and ultrasonographic data with clinical evaluation;

- comparison of the beneficial and harmful effects of the cortisone versus progesterone.

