**Methods:**

Sixty women with age between 18 and 60 years affected by "mild" idiopathic CTS, diagnosed on the basis of clinical and electrodiagnostic tests, will be enrolled in one centre. The clinical, electrophysiological and ultasonographic findings of the patients will be evaluate at baseline, 1, 6 and 12 months after injection.

The major outcome of this study is to determine whether locally-injected progesterone may be more beneficial than cortisone in CTS at clinical levels, tested with symptoms severity self-administered Boston Questionnaire and with visual analogue pain scale.

Secondary outcome measures are: duration of experimental therapy; improvement of electrodiagnostic and ultrasonographic anomalies at various follow-up; comparison of the beneficial and harmful effects of the cortisone versus progesterone.

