### Sample size

The main output parameter is the Symptom Severity Scale (SSS) score of the self-administered Boston Carpal Tunnel Questionnaire. The values reported in the literature assessing the cortisone treatment effect after 2 and 3 months are ranging between 1.37 - 2.3 (mean ± standard deviation: 1.6 ± 0.7). It has been estimated that a minimum number of n = 26.2 subjects for each group would be necessary to reveal a significant (α = 0.05) decrease in the SSS score from 1.6 to 2.0 with enough power (90%). If a drop-out of 4 subjects is considered, the minimum number of subjects required should be adjusted to no. = 30.

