### Data analysis

The values for each recorded parameter (NCV, CSA, BQ, VAS) will be submitted to a two-way ANOVA, with the main factors TREATMENT (cortisol vs progesterone) and TIME (baseline, 1 month, 6 months, and 12 months after the injection). The significance level will be set at *p *< 0.05. Tukey's test post-hoc analysis will be performed when necessary, in order compensate for possible type I errors.

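### The main outcome is SSS alone in the sample-size section but SSS and VAS together in the abstract and design section, with no either/both rule and no error control across the two

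*Protocol article*

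**What the plan says.** All references are to the protocol article.

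- **Sample size:** "The main output parameter is the Symptom Severity Scale (SSS) score of the self-administered Boston Carpal Tunnel Questionnaire". The calculation uses that score only: "to reveal a significant (α = 0.05) decrease in the SSS score from 1.6 to 2.0 with enough power (90"%), with "mean ± standard deviation: 1.6 ± 0.7". VAS plays no part in it.
- **Design of the trial:** the major outcome is to determine that progesterone may be "more beneficial than cortisone in carpal tunnel syndrome at clinical level (SSS-BQ, VAS"). Four secondary outcomes follow. None of them names VAS.
- **Abstract, Methods:** the same pair, with clinical benefit "tested with symptoms severity self-administered Boston Questionnaire and with visual analogue pain scale".
- **Data analysis:** "The values for each recorded parameter (NCV, CSA, BQ, VAS) will be submitted to a two-way ANOVA" with factors TREATMENT and TIME. VAS is named here. SSS is not, and the list has only BQ. Clinical criteria describes that questionnaire as two parts, an 11-item symptom score and an 8-item functional score, each with its own mean.
- **Data analysis, error control:** one level, p < 0.05, applies throughout. The only further provision is "Tukey's test post-hoc analysis will be performed when necessary, in order compensate for possible type I errors".

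**The concern.** The article gives two different definitions of what the trial must show. If SSS and VAS disagree at the end, the Sample size section points to one verdict and the Design section leaves room for another. A non-significant SSS with a significant VAS is a failure under the first and could be presented as success under the second. The choice could then be made after the results are known.

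The safeguard offered does not close this gap. Tukey's procedure compares means within a single ANOVA, here the levels of TIME or the treatment-by-time cells for one parameter. It makes no adjustment between the ANOVA for SSS and the ANOVA for VAS.

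Data analysis also fails to single out the variable on which the trial was sized, because it lists the questionnaire as a whole.

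**Working it through.** **Inputs from the article.** Two outcomes appear in the major outcome, SSS and VAS (Design of the trial; abstract). There is a separate ANOVA for each parameter at p < 0.05, with F tests that have no direction (Data analysis). Sizing is on SSS alone: difference 0.4, SD 0.7, α = 0.05, power 90%, 26.2 per group, raised to 30 for drop-out (Sample size).

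**Inputs assumed.** The article gives no correlation between the SSS and VAS test statistics, so ρ runs from 0 to 0.9. Each outcome gets one two-sided treatment test, and there is no true difference. The two statistics are taken as bivariate normal with critical value c = 1.96.

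**Step 1: the plan's own figure.** The stated 26.2 equals (SD × (z0.95 + z0.90) / difference)² = (0.7 × (1.645 + 1.282) / 0.4)² = 26.2. That is a one-sample, one-sided formula. The two-group formula has a further factor of 2 and gives 53 per arm one-sided or 65 two-sided. This is a separate matter. It matters here only because the 90% used in Step 5 is the plan's claim, not a power I could reproduce for a two-group comparison.

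**Step 2: either outcome suffices, any direction.**
P(at least one significant) = 1 − P(|Z1| < c and |Z2| < c).
At ρ = 0 this is 1 − 0.95² = 0.0975.

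**Step 3: either outcome suffices, false claim favouring progesterone.**
P = 1 − P(Z1 < c and Z2 < c), with the sign set so that positive favours progesterone.
At ρ = 0 this is 1 − 0.975² = 0.0494. One outcome alone gives 0.025.

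**Step 4: both required, any direction.**
P(both) = 0.05 + 0.05 − P(at least one).

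| ρ | Either, any direction | Either, favouring progesterone | Both, any direction |
|---|---|---|---|
| 0 | 9.75% | 4.9% | 0.25% |
| 0.3 | 9.5% | 4.8% | 0.5% |
| 0.5 | 9.1% | 4.5% | 0.9% |
| 0.7 | 8.4% | 4.2% | 1.7% |
| 0.9 | 7.0% | 3.5% | 3.0% |
| One outcome only | 5% | 2.5% | – |

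**Step 5: joint power if both are required.** Suppose each outcome really had the stated 90%. Joint power at ρ = 0 is 0.90 × 0.90 = 81%, and it rises to about 87% at ρ = 0.9. The Sample size section states no effect or SD for VAS, so even the 90% for VAS is a supposition.

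**Step 6: does naming SSS alone restore 5%?** Only if one test decides. Data analysis does not say whether TREATMENT, its interaction with TIME, or a comparison at 1, 6 or 12 months settles the question. If two independent tests on SSS both counted, the rate would again be 1 − 0.95² = 9.75%.

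**The case against.** The strongest reply is that the article already has an anchor. It designates one main parameter and sizes the trial on it, and detailed multiplicity rules usually sit in an analysis plan that is not shown. The second half is fair as far as it goes, because a missing multiplicity rule alone would not be a finding. But the article states two incompatible definitions of its main outcome, and a condensed format does not explain that.

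The reply does stand against several stronger readings that a reader might infer:

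- **That the plan lets either outcome carry the claim.** It does not say so. The abstract joins the two with 'and', so requiring both is an equally natural reading. On that reading there is no inflation. Any error rate must therefore be conditional.
- **That a false claim of progesterone's superiority has a chance of 8-10%.** Figures of that size describe a false difference in either direction, and they need a correlation of at most about 0.75. With non-directional F tests, the false claim for progesterone is 3.5-4.9%. It would reach 6.8-9.75% only if each test were one-sided at 0.05. The sample-size α has no stated side, and the planned ANOVA is not one-sided.
- **That the functional part of the questionnaire gives a third chance.** The abstract and Design section confine the Boston element of the major outcome to symptom severity.
- **That the main effect and the interaction both count as success.** That would raise the rate further, but the article does not say which term decides, so no such figure can be attributed to it.

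**Conclusion.** The point holds as an unreconciled definition of the main outcome with no error control across its two components. One of the stated operating characteristics is left unsupported whenever the Design section governs:

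- **Either outcome suffices:** the chance of at least one false significant difference is about 7-10% instead of 5%. For a false claim favouring progesterone it is about 3.5-4.9% instead of 2.5%. Both ranges are for ρ from 0.9 to 0. In relative terms this is an inflation of about 1.4-fold (7.0/5) to just under 2-fold (9.75/5).
- **Both required:** the error rate is 3.0% or less, but the sample size was not set for joint power.

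The figures rest on an assumed correlation and on one two-sided treatment test per outcome. The contradiction between the sections needs no assumption.

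**What to change.** - **Abstract and Design of the trial:** make SSS the sole primary outcome, as the Sample size section already does. List VAS as the first secondary outcome.
- **Data analysis:** replace BQ by SSS (primary) and the functional score (secondary). Name the one treatment test on SSS that decides, meaning the ANOVA term or contrast and, if relevant, the time point. Test VAS at 0.05 only if SSS is significant. This fixed sequence holds the error across the two outcomes at 5% whatever their correlation, provided that each has one pre-specified test.

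A stated both-required rule or a split α would also remove the ambiguity. Each would call for a new sample-size calculation, whereas SSS alone matches the sizing as written.

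The cost is wording in three places, with no extra data, patients or visits. The small downside is that a result on VAS alone could no longer be presented as success on the major outcome.

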## The Limit

The hydroxyprogesterone caproate is a synthetic steroid hormone which possesses progestational activity in pregnancy to prevent preterm birth. It is a non selective agonist for the classical progesterone receptors because it is able to bind both to androgen and glucocorticoid receptors.

The absence of natural injectable progesterone commercially available could bias our results to some extent.

## Conclusion

Peripheral nerves are able to synthesize and metabolize neuroactive steroids, as progesterone, and are a target for these molecules, since they express classical and non-classical steroid receptors [46]. Progesterone modulate the expression of key transcription factors for Schwann cell function, regulate Schwann cell proliferation and promote the expression of myelin proteins involved in the maintenance of myelin multilamellar structure, such as myelin protein zero and peripheral myelin protein 22. These actions may result in the protection and regeneration of peripheral nerves affected by different form of pathological alterations. Indeed, progesterone is able to counteract biochemical, morphological and functional alterations of peripheral nerves in different experimental models of neuropathy, including the alterations caused by aging, diabetic neuropathy and physical injury.

In our case local corticosteroid injection for CTS is no effective treatment that can stop or reverse median nerve damage and progesterone could to represent really a new therapeutic approach. Therefore the main goal of our study is to show the neuroprotective effects of the progesterone at the level of the peripheral nervous system in humans and "mild" CTS represents a good model.

The results of this trial will be presented as soon as they are available.
